## Abstract

**Background:**

Many patients experience nausea and vomiting during chemotherapy treatment. Evidence demonstrates that electroacupuncture is beneficial for controlling chemotherapy-induced nausea and vomiting (CINV). However, the acupoint or matching acupoint with the best efficacy for controlling CINV still remains unidentified.

**Methods/Design:**

This study consists of a randomized controlled trial (RCT) with four parallel arms: a control group and three electroacupuncture groups (one with *Neiguan* (PC6), one with *Zhongwan* (CV12), and one with both PC6 and CV12). The control group received standard antiemetic only, while the other three groups received electroacupuncture stimulation with different acupoints besides the standard antiemetic. The intervention is done once daily from the first day (day 1) to the fourth day (day 4) during chemotherapy treatment. The primary outcome measures include frequency of nausea, vomiting and retching. The secondary outcome measures are the grade of constipation and diarrhea, electrogastrogram, assessment of quality of life, assessment of anxiety and depression, and other adverse effects during the chemotherapy. Assessments are scheduled from one day pre-chemotherapy (day 0) to the fifth day of chemotherapy (day 5). Follow-ups are done from day 6 to day 21.

**Discussion:**

The aim of this study is to evaluate the efficacy and safety of electro-acupuncture with different acupoints in the management of CINV.

**Trial registration:**

The register number of randomized controlled trial is NCT02195908. The date of registration was 21 July 2014.

## Introduction

### Background

Despite the relevant progress achieved in the last 20 years, chemotherapy-induced nausea and vomiting (CINV) is still one of the most distressing side effects of cancer chemotherapy [1]. As 42 to 52% of patients experience nausea daily during regular treatment, nausea continue to be a significant problem in chemotherapy treatment [2]. *The National Institutes of Health* (*NIH*) 1997 Consensus Statement stated that “promising results have emerged showing efficacy of acupuncture in adult postoperative and chemotherapy nausea and vomiting” [3]. Acupuncture has gained increasing popularity since then as a choice of nonpharmacological adjunctive treatment. Evidence-based medicine demonstrates that electroacupuncture is beneficial towards chemotherapy-induced acute vomiting, and The American Society of Clinical Oncology recommends the usage of electoacupuncture for managing nausea and vomiting in cancer patients [4].

However, no consensus exists on which set of compatible acupoints is optimal, despite trials having been conducted on acupoint matching. Some trials use single acupoints, while others use double acupoints or matching acupoints. For example, Ezzo [5] found that stimulating PC6 may be beneficial for various conditions involving nausea and vomiting, and Shen [6] concluded that electroacupuncture on PC6 (Neiguan) and ST36 (Zusanli) is more effective in controlling emesis than minimal needling or antiemetic pharmacotherapy alone. Hence the answer to the following question remains unknown at present: Which compatible acupoint or acupoints have better efficacy for CINV?

The aim of our study is to evaluate the different efficacies and safety of electroacupuncture on a single point and matching acupoints in the management of chemotherapy-induced nausea and vomiting.

### Hypotheses

According to the theory of Traditional Chinese Medicine (TCM), acupoint compatibility can achieve a synergistic effect. Our prior literature review found that clinically matching acupoints are applied more often than a single acupoint. The pairing of PC6 (Neiguan) with CV12 (Zhongwan) is one of the most commonly used matching acupoints. Our hypothesis is that this pair helps to reduce toxicity and enhance efficacy in the management of chemotherapy-induced nausea and vomiting.

### Objectives

#### Primary objective

Our primary objective in this trial is to assess the clinical efficacy and safety of electroacupuncture on single point or on double points in the management of chemotherapy-induced nausea and vomiting (CINV).

#### Secondary objective

##### Secondary objective

Our secondary objective is to assess the quality of life, anxiety and depression of patients and the other side effects of chemotherapy, such as diarrhea, constipation, *etcetera.*

## Methods/Design

### Trial design

This trial is designed as a four-armed parallel randomized controlled trial.

## Participants

### Eligibility criteria

#### Inclusion criteria

The inclusion criteria include the following:Be diagnosed by histopathology as a tumor patient and accepts chemotherapy.The scoring of Karnofsky (KPS) must be more than 70.Patients of either gender, between 18 to 79 years old inclusive.Patients receiving chemotherapy as outpatients or inpatients.Patients receiving chemotherapy either for the first time or undergoing multiple cycles will be taken into the study only once.Receive cis-platinum (cis-platinum ≥75 mg/m2) or antharcycline combined chemotherapy (doxorubicin ≥40 mg/m2 or epirubicin ≥60 mg/m2)Life expectancy of at least 6 months.Willing to participate in the study and be randomly allocated into one of the four study groups.

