### Allocation and sequence generation

The allocation sequence will be generated by center computer. When the participants voluntarily join this study with informed consents, the practitioner will open the webite (http://iwrs.tice.com.cn/) and evaluate the inclusion and exclusion criteria. If they are accorded with the inclusion criteria, the computer will generate a random number and show which group the participant should be in, and the practitioner will assign the participant to that intervention. The evaluator is blind to which intervention the participant accepts.

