### Randomization

The computer-generated randomization is performed remotely by the Evidence-Based Medicine Center in Tianjin on the website of http://iwrs.tice.com.cn/.

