### Statistical methods

Categorical data will be analyzed with the McNemar chi-square test. We will use analysis of variance (ANOVA) to analyze continuous data. If the data trends over time and over time by treatment interactions, we will choose a repeated-measures analysis of variance (ANOVA). A *P* value less than 0.05 is regarded as statistically significant.

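### Eligibility mixes two regimen classes and first and later cycles, but the stated ANOVA names neither factor; prespecifying both would gain precision and correct chance imbalance

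*Protocol article*

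**What the plan says.** Under Inclusion criteria, two regimen classes are eligible: "Receive cis-platinum (cis-platinum ≥75 mg/m2) or antharcycline combined chemotherapy", with a minimum dose for each drug. The same list accepts patients at any point in their chemotherapy: "Patients receiving chemotherapy either for the first time or undergoing multiple cycles will be taken into the study only once".

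Allocation is covered in two sections. Allocation and sequence generation has the practitioner check eligibility on a website, after which "the computer will generate a random number and show which group the participant should be in". Randomization adds that "The computer-generated randomization is performed remotely by the Evidence-Based Medicine Center in Tianjin". Neither section names a stratum, a block or a minimisation factor.

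Statistical methods gives the model for continuous outcomes: "We will use analysis of variance (ANOVA) to analyze continuous data", with a repeated-measures ANOVA as the alternative when there are trends over time or time-by-treatment interactions. No baseline factor is named for either model. The schedule in Table 1 has a row for baseline variables, but does not say what they are or whether the analysis uses them.

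**The concern.** The main outcome is each patient's number of nausea and vomiting episodes over the six study days. Regimen class and treatment history are plausible sources of variation in that count. The exclusion criteria already remove several competing causes of emesis (opioids, metabolic imbalance, obstruction, brain metastases), whereas these two sources are admitted.

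Both are known before treatment. Regimen class has to be established to enrol a patient at all, and whether this is a first or later cycle is a fact of the history. If they affect the outcome and stay out of the model, two things follow. Their variance remains in the error term of every arm comparison, and any chance imbalance between arms goes uncorrected in the one trial that is run. The Sample size section targets a difference between any two groups, so all six pairwise comparisons are exposed.

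**Working it through.** **Inputs from the article.** Four arms ("This trial is designed as a four-armed parallel randomized controlled trial"); assumed means of 12.5 and 11 with SD 1.5 in each, so a difference of 1.5, or 1.0 SD; power 90%; type I error 5%; 132 patients, raised to 160 for drop-out. The ratio is not stated; equal allocation is assumed, which gives 132/4 = 33 and 160/4 = 40 per arm.

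**Reproducing 132.** Two-sided comparison of two means, Bonferroni over six pairs (alpha = 0.05/6 = 0.00833):
- Normal approximation: n = 2 × (2.638 + 1.282)² × (1.5/1.5)² = 30.7, so 31 per arm (124 in total).
- Noncentral t: 33 per arm, 33 × 4 = 132. This matches the article.

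**Inputs that are assumptions.** The article gives neither the share of patients in each category nor any effect of regimen or cycle. Shares of 30% and 50% are used, with effects of 0.75, 1.5 and 3.0 episodes (0.5, 1 and 2 times the SD of 1.5).

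**Step 1: chance imbalance without strata.** The SD of the difference in share between two arms is sqrt(2p(1−p)/n). A gap of at least 20 points means at least 8 patients at 40 per arm, and at least 7 at 33 per arm (7/33 = 21 points). Simulation of binomial counts in four arms (200,000 runs) gives:

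| n per arm | share p | SD of difference | given pair, 20 points or more | some pair of four, 20 points or more |
|---|---|---|---|---|
| 33 | 0.5 | 0.123 | 0.11 | 0.38 |
| 33 | 0.3 | 0.113 | 0.08 | 0.30 |
| 40 | 0.5 | 0.112 | 0.09 | 0.33 |
| 40 | 0.3 | 0.102 | 0.07 | 0.26 |

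A hand check of one cell (40 per arm, p = 0.5, continuity correction): (7.5/40)/0.112 = 1.68, two-sided probability 0.09.

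**Step 2: what an imbalance does to one result.** Shift = 0.20 × factor effect = 0.15, 0.30 or 0.60 episodes, which is 0.10, 0.20 or 0.40 SD, against a planned difference of 1.5 episodes. One standard error of an arm difference at 40 per arm is sqrt(2/40) = 0.22 SD. The first two shifts are therefore within one standard error.

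**Step 3: precision if SD 1.5 excludes this variation.** A factor with effect g and share 0.5 adds g²/4 to the variance, so total SD = sqrt(1.5² + k × g²/4) for k such factors, taken as independent. Power at 33 per arm (normal approximation) is Φ(sqrt(33/2) × 1.5/SD − 2.638), starting from 92%:
- g = 0.75: SD 1.55 and power 90% with one factor; SD 1.59 and 88% with two.
- g = 1.5: SD 1.68 and 84% with one; SD 1.84 and 75% with two.
- g = 3.0: SD 2.12 and 59% with one; SD 2.60 and 38% with two.

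These are the losses that adjustment would largely recover.

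**Step 4: precision if SD 1.5 already includes it.** Planned power is then not reduced, and adjustment is a pure gain. One factor at share 0.5 explains R² = δ²/4, with δ its effect in total SD: 0.06 at 0.5 SD and 0.25 at 1 SD. With R² of 0.1 to 0.3, the normal-approximation size falls from 31 per arm to between 28 and 22, and power at 33 per arm rises from 92% to between 95% and 99%.

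The article does not say which of Steps 3 and 4 applies.

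**The case against.** The strongest objection is that this rests on silence. Statistical methods is a short summary in a journal article, and covariates are commonly left to an analysis plan, which is not shown here. The allocation text describes what the practitioner sees on the website, and stratified central allocation would look the same from there; the Discussion says a third party designed the system. A reader might infer that the allocation is definitely unstratified and the analysis definitely unadjusted. The article does not say so. It names neither device, and that is as far as the text goes.

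A reader might also infer that an imbalance would be mistaken for an acupoint effect. That does not hold either. Under randomization the unadjusted ANOVA is unbiased on average, and its error term already carries this variation, so the type I error stays valid. Nor is imbalance in a chosen comparison likely: for one given pair it is 7% to 11%, and the 26% to 38% figure refers to the worst of six pairs.

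Finally, no section calls regimen class or cycle prognostic or gives an effect for either. Admitting both is a legitimate choice of population.

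All of this stands as a limit on the claim. What it leaves untouched is that the model as stated is less efficient than one with two readily available factors whenever those factors matter, and that covariates are more credible when fixed before outcomes are seen. Recruitment is already under way.

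**Conclusion.** The point holds as an improvement in precision and in the handling of chance imbalance. It does not show bias or an invalid test.

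Its size depends on effects that the article does not give. At about 0.5 SD per factor the gain is small: roughly two power points for one factor (92% to 90% if left out). At about 1 SD it becomes material: 84% with one factor and 75% with two, if the planning SD excludes this variation. If the planning SD already includes it, the planned power stands and adjustment adds to it. These figures assume equal arms of 33 to 40, categories holding 30% to 50% of patients for the imbalance figures and 50% for the power figures, and a Bonferroni correction over six pairs, which is the reading that reproduces 132.

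**What to change.** Add one sentence to Statistical methods: the between-arm models for continuous outcomes, including the repeated-measures version, contain regimen class (cisplatin or anthracycline) and chemotherapy history (first or later cycle) as prespecified fixed factors. Date it before any outcome data by arm are seen. If the full plan already stratifies or adjusts for these factors, saying so is enough. It would also help to state whether the planning SD of 1.5 refers to a population mixed in regimen and cycle.

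The cost is two degrees of freedom (with 132 patients in four arms, error degrees of freedom go from 132 − 4 = 128 to 126) and making sure that cycle status is among the baseline variables recorded. Regimen class is already established at entry. No change to the ongoing allocation is needed.

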#### Exclusion criteria

Exclusion criteria include the following:Receive radiotherapy concurrently with chemotherapy.Patients with gastrointestinal tumors.Liver disease patients with serious complications, or with serious hepatorenal abnormal function (glutamic oxalacetic transaminase (AST), glutamic-pyruvic transaminase (ALT), or total bilirubin (TBIL) three times higher than normal or blood urea nitrogen (BUN) or urine creatinine (Cr) two times higher than normal).Presence of cardiac pacemaker.Active skin infection.Nausea and/or vomiting as a result from opioids or metabolic imbalance (electrolyte disturbances).Patients unable to provide self-care or communicate, or that have mental sickness,Nausea and/or vomiting resulting from mechanical risk factors (that is, intestinal obstruction).Brain metastases or intracranial hypertension.Women who are pregnant and or lactating.

### Settings and data collection

All the patients are from the Tianjin Medical University Cancer Institute and Hospital. Our trial started on 14 August 2014, and the first participant was recruited on 18 August 2014. The trial is planned to be completed in one year [Figure 1].

**Figure 1 Fig1:**
[figure not shown]
Flow diagram and schedule of enrollment, interventions, and assessments. Assessed for eligibility with eligibility criteria during enrollment, the participants will be randomly divided among four arms: the control group is supplied with a pharmaceutical antiemetic, and the other three arms consist of the antiemetic drug and one type of acupuncture (*Neiguan* (PC6) in one arm or *Zhongwan* (CV12) in another arm), and the antiemetic drug and both types of acupuncture in the remaining arm. The treatment is scheduled to occur within 30 to 60 min before chemotherapy infusion for 4 days. All assessments will be scheduled from the day before chemotherapy to the fifth day of chemotherapy, with follow-up in the next 15 days, followed by data collection and analysis.

### Interventions

There are four arms in this randomized controlled trial. The control group is supplied with antiemetic pharmaceutical, and the other three arms consist of antiemetic drug and acupuncture.

### Control group

The participants in the control group received standard antiemetic alone. Standard antiemetic for all groups is based on *American Society of Clinical Oncology Clinical Practice Guideline* [7]. The 5-hydroxytryptamine-3 (5-HT3) antagonist (Ramosetron, Tropisetron) and dexamethasone are administered before the chemotherapy treatment.

### Experimental group I: single point PC6

Participants in experimental group I will receive electroacupuncture at the *Neiguan* (PC6) point. The location of *Neiguan* (PC6) is on the anterior aspect of the forearm, between the tendons of the palmaris longus and the flexor carpi radialis, 2 B-cun proximal to the palmar wrist crease [8]. After manipulation until a “*de qi*” sensation is achieved, the needle is connected to an electroacupuncture apparatus. The positive pole is linked to the needle, and the reference pole is secured approximately 1 cm proximal to the acupoint with a plaster. The frequency used is 2/10 Hz, and the intensity of stimulation is adjusted according to the patient’s tolerance, with the electric current set at less than 10 mA. The procedure lasts for 30 min. The treatment is scheduled to occur in the 30 to 60 min before chemotherapy infusion for 4 days.

### Experimental group II: single point CV12

The experimental group II will receive electroacupunture at another single point, *Zhongwan* (CV12). The location of *Zhongwan* (CV12) is on the upper abdomen, 4 B-cun superior to the center of the umbilicus, on the anterior median line [8]. After manipulation until a “*de qi*” sensation is achieved, the needle is connected to an electroacupuncture apparatus. The positive pole is linked to the needle, and the reference pole is secured approximately 1 cm proximal to the acupoint with a plaster. The frequency used is 2/10 Hz, and the intensity of stimulation is adjusted according to the patient’s tolerance, with the electric current set at less than 10 mA. The procedure lasts for 30 min. The treatment is scheduled to occur in the 30 to 60 min before chemotherapy infusion for 4 days.

### Experimental group III: matching points PC6 plus CV12

The experimental group III will receive electroacupuncture at both *Neiguan* point (PC6) and *Zhongwan* point (CV12). After manipulation until a “*de qi*” sensation is achieved, the needle is connected to an electroacupuncture apparatus. The positive pole is linked to the needle, and the reference pole is secured approximately one cm in the proximity of the acupoint with a plaster. The frequency used is 2/10 Hz, and the intensity of stimulation is adjusted according to the patient’s tolerance, with the electric current set at less than 10 mA. The procedure lasts for 30 min. The treatment is scheduled to occur in the 30 min to 60 min before chemotherapy infusion for 4 days.

### Outcomes

#### Primary outcome

The primary outcomes are as follows:The frequency of nausea and vomitingTotal nausea and vomiting episodes per person over the 6-day study period will be recorded. The frequency of nausea and vomiting is the measurement with the most value for evaluation.The grading of nausea and vomitingThe Common Terminology Criteria for Adverse Events Version 4.0 [9] will be used to grade the nausea and vomiting.Rhodes Index of Nausea, Vomiting and RetchingThe Rhodes Index of Nausea, Vomiting and Retching [10], an eight-item validated scale, will be used to measure the nausea and vomiting experience, incidence and severity.

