### Participant timeline

The enrollment will be done before the day of chemotherapy on day zero. The electroacupuncture intervention will be given once daily from day one to day four. All assessments will be scheduled from day zero to day five (see Table 1).

**Table 1 Tab1:** The schedule of enrollment, interventions, and assessments

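### By its natural reading the leading primary outcome, total episodes over six days, includes day 0, before chemotherapy and electroacupuncture, which adds noise but not bias

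*Protocol article*

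**What the plan says.** The Primary outcome section lists three outcomes. For the first, total nausea and vomiting "episodes per person over the 6-day study period will be recorded". The same section ranks it above the other two: "The frequency of nausea and vomiting is the measurement with the most value for evaluation". It does not name the six days.

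Other sections give the calendar:

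- Participant timeline: "All assessments will be scheduled from day zero to day five", and for day 0 itself, "The enrollment will be done before the day of chemotherapy on day zero".
- Figure 1 caption: "All assessments will be scheduled from the day before chemotherapy to the fifth day of chemotherapy".
- Abstract, Methods/Design: the same span, day 0 to day 5, with days 6 to 21 assigned to follow-up.
- Participant timeline, on treatment: "The electroacupuncture intervention will be given once daily from day one to day four".
- Table 1: the frequency row is marked in the column headed 0 (allocation), at t1 to t5, and at t6 (day 21).

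Statistical methods plans ANOVA for continuous data, with repeated-measures ANOVA as a conditional option. It names no baseline adjustment. No section says that day 0 is left out of the total or kept as a baseline only.

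**The concern.** The trial is about nausea and vomiting caused by chemotherapy, and whether electroacupuncture reduces it. A total that starts on day 0 counts one day on which neither cause nor remedy has been applied. Day 0 need not be free of symptoms, because the Inclusion criteria admit patients in later cycles: "Patients receiving chemotherapy either for the first time or undergoing multiple cycles will be taken into the study only once". Anticipatory symptoms, or symptoms left from an earlier cycle, are therefore possible, and the Exclusion criteria do not remove them.

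At stake is precision in the outcome that the article values most. Day-0 variation enters the error term of the between-group comparison and carries no treatment effect. The same count would do more good as a covariate.

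**Working it through.** **Step 1. Which six days?** Day 0 to day 5 is 5 − 0 + 1 = 6 days. Day 1 to day 5 is 5 days. Day 6 onward is follow-up. Table 1 also has six marks from t1 to t6, but t6 is day 21, so those are not a six-day period. Only day 0 to day 5 fits.

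**Step 2. Can day 0 carry a treatment effect?** Enrolment is on day 0, before the day of chemotherapy. The first session is on day 1, in the hour before infusion. So the expected difference between arms on day 0 is zero, and the expected difference in the six-day total equals that in the five-day total. Only the variance changes.

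**Step 3. Reproduce the plan's sample size.** Inputs from Sample size: means 12.5 and 11 (difference 1.5), SD 1.5 in both groups, power 90%, type I error 5%, any two of the four groups. Equal allocation is assumed. For a two-sample t-test with standardised difference 1.5/1.5 = 1.0:

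- Two-sided alpha 0.05: 22.02, so 23 per arm and 4 × 23 = 92. This does not match 132.
- Two-sided alpha 0.05/6 (six pairs of groups): 32.51, so 33 per arm and 4 × 33 = 132. This matches.

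The article does not state the division by six. It is inferred from the match.

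**Step 4. Effect of adding day 0.** Assume that 1.5 is the SD of the days 1 to 5 total. With s₀ the day-0 SD and ρ its correlation with that total,

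SD of six-day total = √(1.5² + s₀² + 2ρ × 1.5 × s₀).

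For example, s₀ = 0.5 and ρ = 0.3 give √(2.25 + 0.25 + 0.45) = √2.95 = 1.718. Power is from the noncentral t distribution, difference 1.5, 33 per arm, two-sided alpha 0.05/6. The values of s₀ and ρ are assumptions, since the article gives neither.

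| Assumed day-0 SD | SD of total, ρ = 0 | Power, ρ = 0 | SD of total, ρ = 0.3 | Power, ρ = 0.3 |
|---|---|---|---|---|
| day 0 left out | 1.500 | 90.5% | 1.500 | 90.5% |
| 0.1 | 1.503 | 90.4% | 1.533 | 89.0% |
| 0.25 | 1.521 | 89.6% | 1.593 | 86.0% |
| 0.5 | 1.581 | 86.6% | 1.718 | 79.2% |
| 1.0 | 1.803 | 74.2% | 2.037 | 60.7% |

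**Step 5. Is the last row plausible?** If the five-day total has SD 1.5 and the days are independent with equal variance, one chemotherapy day has SD 1.5/√5 = 0.67. If the days correlate at 0.3, it is √(2.25 / (5 × (1 + 4 × 0.3))) = √(2.25/11) = 0.45. A day-0 SD of 1.0 would make the day without chemotherapy 1.5 to 2.2 times as variable as an average chemotherapy day. I give that row as an outer bound and do not rely on it.

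**Step 6. Sensitivity to alpha.** At two-sided 0.05 with 33 per arm, power without day 0 is 97.9%. For s₀ of 0.5 to 1.0 it is 96.7% to 91.4% when ρ = 0 and 93.7% to 83.8% when ρ = 0.3. Only the most extreme of these four cases falls below 90%.

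**The case against.** The strongest reply is that the article never says day 0 is summed into the tested value. It says that episodes will be recorded, which describes data capture, and an analysis plan that is not shown could set day 0 aside. It is true that the inclusion is inferred. But the article itself fixes the window at six days, and five days of treatment-period data do not fill it. If day 0 was never meant to count, the stated length is wrong and the same sentence needs changing.

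Second, the conditional repeated-measures ANOVA would treat day 0 as a separate time point and not as part of a sum. That is right for that analysis. It does not help the outcome as defined, a single total per person.

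Third, the power loss depends on choices. The alpha of 0.05/6 is not stated, the day-0 SDs are assumed, and Sample size does not say which days its emesis number covers. If 1.5 is already the SD of the six-day total, there is no loss against the plan. All of this stands. The Exclusion criteria also remove several other sources of nausea, such as opioids, metabolic imbalance and obstruction, which makes a low day-0 count more likely.

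A reader might infer more than the article supports:

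- That the comparison is biased. It is not: randomisation gives the arms the same expected day-0 count. Chance imbalance on day 0 is the same harm as the added variance and already lies within the standard error, so it is not a second harm.
- That the outcome no longer measures chemotherapy-induced symptoms. Five of its six days do.
- That the baseline is lost. Table 1 records it separately.
- That the Rhodes Index and toxicity grades share the fault. No summary of them over day 0 to day 5 is defined.

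**Conclusion.** The point holds as a matter of precision and clarity. By its natural reading, one of the six days counted in the leading primary outcome lies outside both chemotherapy and intervention. It adds noise and cannot add signal.

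The size cannot be computed from the article. Under the assumptions in the working (SD 1.5 for days 1 to 5, 33 per arm, inferred alpha 0.05/6), the cost is about 1 to 4.5 points of power for a day-0 SD of 0.25 and about 4 to 11 points for 0.5. It is negligible if day-0 episodes are rare. The stated 132 and 160 are not shown to be wrong by this point. The change is worth making because it costs almost nothing, not because the trial is compromised without it.

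**What to change.** In Primary outcome, replace the unnamed six-day period with named days: the primary frequency is the total number of episodes per person from day 1 to day 5. State that the day-0 count is used only as a baseline covariate in the between-group comparison, for example by analysis of covariance in place of plain ANOVA.

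The cost is one sentence in the outcome definition and a few words in Statistical methods. Table 1 already schedules the count separately at each time point, so no new data and no extra patients are needed. The article reports that recruitment is under way, so the change should be dated and made before any unblinded analysis.

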### Sample size

Sample size calculation has been based on the result of a trial by *Shen J* [6] and the recommendation of acupuncture specialists in China. The mean value of emesis number in the Neiguan group is 12.5, the standard deviation is 1.5, and the mean value of emesis number in Neiguan plus Zhongwan group is 11, the standard deviation is 1.5. To detect a significant difference between any two groups with a power of 90% and type I error of 5%, the calculated number of patients is 132. Considering a 20% drop-out rate, the total sample size needs 160 patients.

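### Three primary outcomes share one unadjusted 0.05 threshold with no success rule, and the stated 90% power is for emesis number, at most the vomiting part of the lead outcome

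*Protocol article*

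**What the plan says.** Under Primary outcome, the protocol article lists three outcomes.

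- **Frequency of nausea and vomiting:** total episodes per person over the 6-day study period. The article adds: "The frequency of nausea and vomiting is the measurement with the most value for evaluation".
- **CTCAE version 4.0**, which "will be used to grade the nausea and vomiting".
- **Rhodes Index of Nausea, Vomiting and Retching**, "an eight-item validated scale, will be used to measure the nausea and vomiting experience, incidence and severity".

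The abstract puts it more briefly: "The primary outcome measures include frequency of nausea, vomiting and retching".

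Statistical methods has one decision rule for everything: a P "value less than 0.05 is regarded as statistically significant".

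Sample size rests on one variable in two of the four arms: "The mean value of emesis number in the Neiguan group is 12.5, the standard deviation is 1.5". For the arm that combines both acupoints, the assumed mean is 11 and the SD is unchanged. The stated aim is "To detect a significant difference between any two groups with a power of 90% and type I error of 5" per cent, which gives 132 patients, raised to 160 for 20% drop-out. No mean, SD or effect is given for nausea episodes, for nausea and vomiting together, for the CTCAE grade or for the Rhodes Index.

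**The concern.** Two things that the article fixes do not fit together.

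First, three outcomes carry primary status under one flat threshold, and nothing says what counts as a positive trial. If one significant result is enough, the error rate for the primary claim exceeds the 5% used to size the trial. If all three are needed, error is controlled, but the chance of success is lower than the power of any single outcome, and the article does not give it.

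Second, the variable behind the 90% power is not the one the article ranks highest. Emesis number is at most the vomiting part of the frequency outcome. A reader would take the 90% as the trial's chance of detecting a difference in its lead outcome, and the article does not show that.

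**Working it through.** **1. The plan's own figure.** Inputs from Sample size: difference 12.5 − 11 = 1.5; SD 1.5; standardised effect 1.5/1.5 = 1.0; power 90%; type I error 5%. Two-sided testing and equal allocation to four arms are assumed, since neither is stated.

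| Two-sided two-sample t-test | n per arm | Four arms |
|---|---|---|
| alpha 0.05 | 23 | 92 |
| alpha 0.05/6 = 0.00833 | 33 | 132 |

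The second row gives the stated 132 exactly, with power 0.905. The six is the number of pairs among four groups (4 × 3/2). So the calculation appears to allow for six group comparisons, but not for three primary outcomes.

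**2. Error rate if any one outcome suffices.** With one four-group test per outcome at 0.05 and independent outcomes, the chance of at least one false positive is 1 − 0.95³ = 1 − 0.857 = 0.143.

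The three outcomes describe the same symptoms in the same patients, so they will be correlated. Simulating four arms of 33 with three equally correlated normal outcomes, no true differences and one ANOVA F test each gives:

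| Correlation | At least one false-positive primary |
|---|---|
| 0 | about 14% |
| 0.5 | about 13% |
| 0.8 | about 10% |
| 0.9 | about 9% |

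The CTCAE grade is ordinal, so the normal model is an approximation.

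**3. Power if all three must succeed.** Suppose, for illustration only, that each outcome had 90% power. Joint power would be 0.9³ = 0.73 if they were independent, rising to 0.90 if they were perfectly correlated. The article gives no inputs for a real calculation.

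**4. Power for the lead outcome.** The article gives no figures for it. Keep the difference of 1.5 and 33 per arm, and let the SD vary over an assumed range. Power comes from the noncentral t distribution with noncentrality (1.5/SD) × √(33/2) and 64 degrees of freedom:

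| SD | Power at alpha 0.05 | Power at alpha 0.05/6 |
|---|---|---|
| 1.5 (the article's value for emesis) | 0.98 | 0.91 |
| 2 | 0.85 | 0.63 |
| 2.5 | 0.67 | 0.39 |
| 3 | 0.52 | 0.25 |

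**5. Cost of keeping three primaries.** The strictest Bonferroni step over 3 outcomes × 6 pairs is 0.05/18 = 0.00278. At a standardised effect of 1.0 this needs 39 per arm, or 156 evaluable; power at 33 per arm is 0.82. For one prespecified pair the step is 0.05/3 = 0.0167, which needs 29 per arm (116 in total), within the planned 132.

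**The case against.** The strongest reply is that the article never says one significant outcome is enough. A success rule and multiplicity adjustment often sit in a statistical analysis plan, which is not shown here. The article also ranks frequency first, which limits later choice among outcomes. This stands in part: the 9% to 14% is conditional on an any-one rule and cannot be stated as the trial's error rate. But three primaries and a flat threshold are what the article itself fixes, and a remark about value is neither a testing order nor a demotion of the other two. The gap between the powered variable and the lead outcome is in the text and does not depend on an unseen document.

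A reader might infer four stronger points, which the article does not support.

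- **Nausea and vomiting episodes are summed, so one bout can count twice.** The wording can equally mean two counts, each totalled. On that reading emesis number is one component of the lead outcome, so it would be too strong to call it unrelated to every listed primary.
- **The abstract contradicts the outcomes section.** It says the primary measures include certain frequencies, which may only be condensing.
- **The error rate is 36% to 49%.** Those figures need six unadjusted pairwise tests on each outcome. Most of that excess comes from the group comparisons, a separate issue, and the 132 suggests the planners had them in mind.
- **Vomiting should become the sole primary, as a mere wording change.** That would reverse the investigators' own ranking during recruitment.

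**Conclusion.** The point holds in a limited form. The article sets three primary outcomes, one unadjusted threshold and no rule for success. If any one suffices, the false-positive chance for the primary claim is about 9% to 14% rather than 5%, assuming one four-group test per outcome, approximate normality and correlations from 0.9 to 0. If all must succeed, error does not inflate but joint power is unknown.

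The 132 is not itself in error: it reproduces for emesis number with alpha divided over six pairs. What is unsupported is carrying its 90% power over to any listed primary outcome. For the lead outcome, power at 33 per arm could be 0.85 to 0.52 at alpha 0.05, or 0.63 to 0.25 at 0.05/6. That rests on an assumed SD of 2 to 3 with the difference unchanged; a larger difference in the lead outcome would raise it.

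**What to change.** Make a dated amendment before any comparison of outcomes by arm.

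- **Preferred:** make the frequency outcome, which the protocol already ranks highest, the single primary. Move the CTCAE grade and then the Rhodes Index to key secondary outcomes, tested in that fixed order.
- **Alternative:** keep all three as primary and apply Holm across them.
- **In either case:** state exactly how the frequency outcome is counted, and report nausea and vomiting episodes separately. Restate the power in Sample size as applying to vomiting episodes only, or give the mean, SD and difference assumed for the chosen primary. Use the same definition in the abstract, Primary outcome and Sample size.

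All measures are still collected. The costs are real, though. CTCAE and Rhodes results become secondary evidence, or all three primaries face a stricter threshold. The power statement will probably look less favourable. The first participant was recruited on 18 August 2014 and Trial status reports ongoing recruitment, so a protocol and registry amendment is needed mid-trial.
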